#### AAQoL—health-related quality of life

The AAQoL is a measure of health-related quality of life (HRQoL) that investigates quality of life and function among adults with ADHD. The AAQoL consists of 29 questions measuring HRQoL over the previous 2 weeks. The original version of the AAQoL has exhibited satisfactory psychometric properties in previous studies [30–32]. The Norwegian version has previously been validated by our research group and was found to fit well with the original version [33].

### Statistics

Statistical analysis will be conducted using SPSS [34] and STATA [35]. In order to calculate preliminary effects, chi-square statistics and *t* tests will be used for descriptive analyses of categorical and continuous variables, respectively, in addition to analysis of variance (ANOVA) for comparison of results for the control and experimental groups. Possible other predictors for the preliminary efficacy of psychoeducation will be examined using linear regression on the total sample (pre-post intervention). Intervention adherence will be calculated by assessing the response rate of participants receiving the intervention, response rate of returned questionnaires, and the number of sessions completed by intervention group participants. Recruitment and dropout rates will be evaluated using absolute and percentage frequencies.

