Even though the results of these studies are promising, more controlled trials are needed to assess the efficacy of psychoeducation for adults with ADHD. Thus, there is a necessity to evaluate patient satisfaction and the short-term effects of psychoeducational group interventions in clinical settings. This study protocol describes an innovative education group intervention where health personnel and representatives from the ADHD user organization educate adults with ADHD to improve self-management. User involvement will occur during the intervention delivery phase. Representatives from user organizations will be peer educators co-leading two sessions. The intervention will be delivered at two centers, of which the center that has developed the intervention has limited experience with the research procedures needed to conduct a proper trial. The other center has no previous experience delivering the intervention. In order to plan a definitive trial, we must investigate the feasibility of both the research and intervention procedures, as well as evaluate patient satisfaction within the context of the intervention. We require information on how many patients will complete the intervention with evaluable data, as well as insight into the feasibility of randomization procedures and estimates of parameters required for sample calculation. This intervention is based on active participation and exchange of experiences between the participants. Measuring patient satisfaction is also an important part of fine-tuning the intervention before a large-scale trial. Hence, the purpose of our study was to investigate the feasibility, preliminary effects, and patient satisfaction with a group-based psychoeducational program consisting of ten sessions delivered to adults with ADHD using a prospective, randomized, and controlled study design.

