## Methods

### Study design

This protocol describes a multicenter trial to study patient satisfaction and the preliminary efficacy of a group-based psychoeducational program for adults with ADHD and is available online at ClinicalTrials.gov (NCT03337425). The study will be reported in accordance with the Template for Interventions Description and Replication and the Consolidated Standards of Reporting Trials.

Patients from two different outpatient clinics (Nord-Trøndelag Hospital Trust and Tiller District Psychiatric Centre) will be included. The treatment is available for patients in the Nord-Trøndelag Hospital Trust for 4 years, but it has not been evaluated nor has it been implemented at the other center. Therefore, a pilot study is warranted. All patients included in the study will receive treatment as usual concomitant to psychoeducation or waitlist. Patients will be recruited and randomly assigned to condition A, psychoeducation + treatment as usual, or condition B, waiting list + treatment as usual. There is a need for at least 30 subjects in each cohort. Eligible outpatients diagnosed with ADHD at one of the outpatient clinics could be enrolled. The inclusion and exclusion criteria are listed in Table 1, and the recruitment procedure and assignment to conditions are found in Fig. 1.

**Table 1 Tab1:** Inclusion and exclusion criteria

Inclusion criteria	Exclusion criteria
Age between 18 and 67	Unable to give informed consent
Speaking a Scandinavian language	Psychosis
Confirmed ADHD diagnosis	Severe learning difficulties

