### Data and measurement

Clinical symptoms and function will be measured at the time of recruitment prior to randomization (T0), pre-intervention (T1), post-intervention (T2) as well as at 10 weeks follow-up (T3). The waitlist-control group will have two additional measurements during the pre- and post-waiting period. Measuring patient satisfaction and change in symptom load, general self-efficacy, quality of life, and function can serve as indicators of the preliminary efficacy of the intervention. The assessments and measurements are listed in Fig. 2.

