### Sample size

This project is intended to evaluate the feasibility of implementing an educational group intervention led in co-operation with health personnel and peer educators to inform an eventual larger-scale randomized study that will allow for a more rigorous assessment of the impact of the intervention. Hence, our sample size is driven primarily by practical issues related to the number of patients needed to enroll at each site, opinions about the questionnaires, and satisfaction with the intervention. Consequently, the anticipated sample will be 60 patients—30 patients in each arm. The chosen sample size is also in accordance with the median number of participants observed in an audit of pilot and feasibility trials in the UK [36].

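### The arm comparison is planned as ANOVA without adjustment for the pre-randomization T0 score, which gives up precision and leaves chance baseline imbalance in the estimate

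*Protocol article*

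**What the plan says.** The Statistics section of the protocol article assigns three roles:

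- Description: "chi-square statistics and *t* tests will be used for descriptive analyses of categorical and continuous variables, respectively".
- The randomized contrast: "analysis of variance (ANOVA) for comparison of results for the control and experimental groups". The type of ANOVA is not given, and no covariate is named.
- Regression: "Possible other predictors for the preliminary efficacy of psychoeducation will be examined using linear regression on the total sample (pre-post intervention"). This is a search for predictors in the pooled sample, not the comparison of arms.

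Under Data and measurement, the baseline is defined: "Clinical symptoms and function will be measured at the time of recruitment prior to randomization (T0"). The same paragraph gives the waitlist arm additional measurements before and after waiting, so an end-of-waiting score exists to set against the end-of-intervention score.

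The Sample size section states that "the anticipated sample will be 60 patients—30 patients in each arm", on practical grounds. The section on the main study and decision to proceed bases that decision partly on preliminary efficacy for symptoms and quality of life. The Background says the pilot must supply parameters for a later sample-size calculation.

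**The concern.** ASRS (two subscores), SCL-9, AAQoL and GSE-6 all have a T0 value that allocation cannot have influenced. In a two-arm trial of this size, that value is usually the strongest available predictor of the later score. The method named for the arm comparison gives it no covariate role.

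Two things are at stake. The effect estimate, which helps decide whether a main trial goes ahead, has a wider interval than the trial's own data allow. In any single realized trial, the estimate also carries part of whatever T0 difference chance has produced between the arms. Because the sample was fixed on practical grounds, the analysis is the cheapest place to gain precision.

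**Working it through.** **Plan's own figure.** 30 + 30 = 60 is consistent. No alpha, power, effect size or SD is stated, so there is no power calculation to reproduce.

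**Inputs from the document.** 30 per arm; T0 before randomization; ANOVA for the arm comparison.

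**Assumed, not in the document.** Correlation r between T0 and the outcome of 0.3 to 0.7; equal SDs at both visits; a true effect of 0.5 SD and two-sided alpha of 0.05 for the power figures; no dropout; independent patients.

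**Step 1: chance imbalance at T0.** SE of the difference = sqrt(2/30) = 0.258 SD. From the normal distribution, P(|difference| > 0.25 SD) = 33%, P(> 0.3 SD) is about 25%, and P(> 0.5 SD) is about 5%.

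**Step 2: how much reaches the estimate.** Given a T0 difference D, an unadjusted follow-up contrast shifts by r × D and a change-score contrast by −(1 − r) × D. For D = 0.25 SD and r = 0.3 / 0.5 / 0.7:

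- follow-up: 0.08 / 0.13 / 0.18 SD in the direction of D;
- change score: 0.18 / 0.13 / 0.08 SD in the opposite direction.

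ANCOVA on T0 removes this shift when the relation is linear.

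**Step 3: precision.** In outcome-SD units, the variance of the arm difference is (2/30) × factor. The factor is 1 for the follow-up score, 2(1 − r) for a change score or a group-by-time ANOVA on T0 and the end score, and 1 − r² for ANCOVA. The 95% half-width is 1.96 × sqrt((2/30) × factor).

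| | r = 0.3 | r = 0.5 | r = 0.7 |
|---|---|---|---|
| Factor, follow-up | 1.00 | 1.00 | 1.00 |
| Factor, change or group-by-time | 1.40 | 1.00 | 0.60 |
| Factor, ANCOVA | 0.91 | 0.75 | 0.51 |
| Half-width, follow-up (SD) | 0.51 | 0.51 | 0.51 |
| Half-width, change (SD) | 0.60 | 0.51 | 0.39 |
| Half-width, ANCOVA (SD) | 0.48 | 0.44 | 0.36 |
| Power at 0.5 SD, follow-up | 49% | 49% | 49% |
| Power at 0.5 SD, change | 37% | 49% | 71% |
| Power at 0.5 SD, ANCOVA | 53% | 61% | 77% |

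Power is by normal approximation; t-based values are one to two points lower.

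Variance reduction by ANCOVA:

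- against follow-up, r²: 9% / 25% / 49%;
- against change, 1 − (1 + r)/2: 35% / 25% / 15%.

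To match ANCOVA with 60 patients, the follow-up comparison would need 60/(1 − r²) = 66 / 80 / 118 patients. The change-score comparison would need 60 × 2/(1 + r) = 92 / 80 / 71.

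**Step 4: centre.** This was simulated with 5,000 trials per scenario, equal centre sizes, and a centre shift of 0 or 0.5 SD. Adding centre to the T0-adjusted model changed the empirical SE by at most 0.002 SD (0.229 with and without it at r = 0.5 and a shift of 0.5 SD). Essentially all the gain comes from T0.

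**The case against.** The strongest reply is that a condensed article commonly leaves covariates and model details to an analysis plan that is not shown, and that the Statistics section does not forbid adjustment. It is true that such a plan may refine the model. But the section names a method for the arm comparison, and that method as stated is less precise than one using data already collected. Reading the ANOVA as group-by-time does not rescue it: (1 + r)/2 is below 1 for every r below 1.

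The second reply is that this is a pilot with no power calculation and no stated efficacy threshold, so modest extra precision would tip nothing formally. This stands as a limit on severity. It does not remove the point, because the estimate feeds the decision to proceed.

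Several stronger readings are tempting but not supported:

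- *The t tests estimate the effect.* The text calls them descriptive; ANOVA carries the comparison.
- *The planned analysis is invalid or biased.* Follow-up and change-score contrasts are both unbiased over repeated randomization.
- *Large imbalance is to be expected.* A T0 gap above 0.5 SD arises in only about 5% of trials.
- *Omitting centre costs precision.* There are two clinics, and "The other center has no previous experience delivering the intervention". That is a design reason to include centre, but the simulation shows no useful gain once T0 is in the model.
- *The SD handed to the main trial will be too large.* The document does not say which SD will be used. A raw SD is right for an unadjusted main analysis and too large only if the main trial uses ANCOVA.
- *T1 will be used as the baseline.* Nothing says so. The point is only that T0 alone is stated to precede randomization.

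**Conclusion.** The point holds as one of efficiency and conditional bias, of moderate weight. The named ANOVA ignores T0 or, if group-by-time, uses it less well than ANCOVA would. Across r = 0.3 to 0.7 the avoidable variance is 9% to 49% against a follow-up comparison and 35% to 15% against a change-score one.

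The direction does not depend on the assumed r, apart from the small cost in degrees of freedom. The size does: at r = 0.3 the gain over a follow-up comparison is small (power 49% to 53%). The power figures also rest on the assumed 0.5 SD effect. All figures take patients as independent, although the programme is delivered in groups, and assume no dropout.

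**What to change.** In the Statistics section, state that for each continuous outcome measured at T0 the between-arm effect comes from a linear model (ANCOVA). The outcome is the end-of-intervention score in arm A and the end-of-waiting score in arm B; the terms are arm and the T0 value of the same score. Report the adjusted difference with its 95% CI.

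Name T0, not T1, as the covariate. Centre may be added as a design factor, without claiming a precision gain for it. For main-trial planning, report the raw SD together with the T0-outcome correlation (or the ANCOVA residual SD), so that the later calculation can match whichever analysis is chosen.

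The cost is one sentence on the model plus a reporting line, one degree of freedom for T0 and one more if centre is included. No new data are needed.

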#### Condition A: Psychoeducation concomitant with treatment as usual

Both conditions A and B received treatment as usual (see description under the “Condition B: Waiting list concomitant with treatment as usual” section) in addition to psychoeducation or waitlist. The group-based psychoeducational program consists of ten sessions that were ran over ten consecutive weeks. Each session consists of a lecture from a recruited expert on the topic of the session (20 min) with a following discussion of the topic (45 min) facilitated by the course leader (Table 2). All sessions are organized and led by the course leader, which also includes structured time, discussion, and closing of the session.

**Table 2 Tab2:** Topic for sessions

Topic and main focus for session	Lecturer (in addition to course leader)
Introduction and presentation of the intervention Myths and facts about ADHD	Given by the course leader (nurse) and expert in ADHD (social worker or psychologist)
What is ADHD?	Nurse or social worker or psychologist with ADHD expertise
Inattention	Nurse or social worker or psychologist with ADHD expertise
Impulsivity	Nurse or social worker or psychologist with ADHD expertise
Hyperactivity	Nurse or social worker or psychologist with ADHD expertise.
ADHD and comorbidity	Medical doctor, psychologist, or experienced psychiatric nurse
Use of medications	Medical doctor specialized in ADHD
Economy	Social worker
Work and welfare	Representative from the public welfare agency Representative from ADHD Norway
Summary and closing session	Led by the course leader

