### Methodological strengths

To the best of our knowledge, this will be the first pilot randomized, waitlist-controlled, multicenter trial of a psychoeducational intervention for patients with adult ADHD. All participants will be recruited from outpatient clinics. These are patients with a confirmed diagnosis. The treatment is delivered in outpatient clinics and will therefore increase the ecological validity of the study within a Norwegian health care context. The outcome measurements will be based on validated instruments and well-tested in international research as well as in clinical practice. This offers useful data both for research and the clinic. Translated instruments are validated and published in international peer-reviewed journals. We used a multicenter intervention and different course leaders and lecturers to reduce the effect of individual therapeutic factors. This offers more reliable evidence on the specific effects of the intervention content.

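### The arms are compared with ANOVA, which treats patients as independent, although only the treated patients are nested in interacting groups; if the within-group correlation is positive, the standard error of the arm difference is understated

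*Protocol article*

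**What the plan says.** The Statistics section assigns the between-arm comparison to "analysis of variance (ANOVA) for comparison of results for the control and experimental groups". It also mentions t tests and chi-square statistics, but labels them descriptive. The article names no term for therapy group, no mixed model, no cluster-robust standard error and no ICC.

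The treated arm is delivered in groups. The section on condition A states: "The group-based psychoeducational program consists of ten sessions that were ran over ten consecutive weeks". Each session has a lecture "with a following discussion of the topic (45 min) facilitated by the course leader". The Background adds: "This intervention is based on active participation and exchange of experiences between the participants". Methodological strengths reports: "We used a multicenter intervention and different course leaders and lecturers to reduce the effect of individual therapeutic factors". The section on condition B tells waitlist patients to carry on with their ordinary lives and treatment, so they belong to no group while the arms are being compared.

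The Background also lists, among the reasons for the pilot, "estimates of parameters required for sample calculation". The section on the main study and the decision to proceed says that the main trial will have the same design, and that preliminary efficacy is one basis for going ahead.

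**The concern.** Patients who spend ten weeks in the same group share a course leader, lecturers, discussions and one another. Their outcomes at T2 are likely to be more alike than those of patients in different groups, and here interaction is part of how the treatment is meant to work. Waitlist patients have no such link. The design is therefore partially nested: clustered in one arm, not in the other. An ANOVA on individual patients counts 30 treated patients as 30 independent pieces of information, which is too many if the ICC is positive.

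Two uses of the result make this matter even in a pilot. The preliminary effect enters the decision to proceed, and the pilot is meant to supply sample-size parameters for a main trial of the same group-delivered design. For such a trial the ICC is one of those parameters.

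**Working it through.** **Inputs from the article.** 60 patients, 30 per arm (Sample size); 2 × 30 = 60 agrees. The sample size is set on practical grounds, with no alpha, power, effect size or standard deviation, so there is no power-based figure to reproduce.

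**Assumptions.** Group size *m* from 7.5 (four groups in the treated arm) to 15 (two groups). ICC 0.01, 0.05 and 0.10. Equal total variance SD² in both arms. Nominal two-sided level 0.05.

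**Formulas.**
- Variance of the arm difference under ANOVA: 2 × SD²/30, which gives a standard error of 0.258 SD.
- Variance with clustering in the treated arm only: (SD²/30) × [1 + (1 + (m − 1) × ICC)].
- Variance ratio: R = [2 + (m − 1) × ICC]/2.
- Actual type I error of the unadjusted test: 2 × [1 − Φ(1.96/√R)].

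**Numbers put in.** For m = 15 and ICC 0.05: R = (2 + 14 × 0.05)/2 = 1.35; √R = 1.162; 1.96/1.162 = 1.687; type I error 0.092.

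| m | ICC | R | SE ratio √R | Type I error |
|---|---|---|---|---|
| 7.5 | 0.01 | 1.03 | 1.016 | 0.054 |
| 15 | 0.01 | 1.07 | 1.034 | 0.058 |
| 7.5 | 0.05 | 1.16 | 1.078 | 0.069 |
| 15 | 0.05 | 1.35 | 1.162 | 0.092 |
| 7.5 | 0.10 | 1.33 | 1.151 | 0.089 |
| 15 | 0.10 | 1.70 | 1.304 | 0.133 |

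**Check by simulation.** With 40,000 simulated trials per scenario and groups of 15, the unadjusted two-sample test (equivalent to a two-group ANOVA) rejected in 5.9%, 8.9% and 13.5% of null trials at ICC 0.01, 0.05 and 0.10. The formula gives 5.8%, 9.2% and 13.3%.

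**What the pilot can learn about the ICC.** With a true ICC of 0.05 and three groups of 10 in one arm, the central 95% of simulated ICC estimates ran from about −0.11 to 0.36. With both arms eventually treated (six groups of 10), it was about −0.08 to 0.25.

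**Illustration for the main trial.** Assume a standardised difference of 0.5, 80% power and two-sided 0.05. Ignoring clustering, 63 per arm are needed. Multiplying by R and rounding up, groups of 15 need 68 (ICC 0.01), 86 (0.05) or 108 (0.10) per arm.

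**The case against.** The strongest reply has four parts.

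1. *This is a condensed article, and an analysis plan may contain a group term.* That is possible, and the absence of a group identifier or random effect from the article is not in itself the point. The point is that the article names a specific method for the arm comparison and, as named, that method does not fit the delivery it describes.

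2. *The understatement needs a positive ICC, and none is given.* This stands. At ICC 0.01 the type I error stays below 6%, which is negligible in a pilot.

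3. *The harm is limited.* The article states no significance threshold for proceeding, leaves rigorous assessment to the larger trial, and nowhere says that the main trial will be sized without a design effect. This also stands, and it keeps the point well short of a fatal flaw.

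4. *A random group effect cannot be estimated well from two to four groups.* Correct. With two groups at two centres, group and centre could even coincide. The mixed model therefore cannot carry the main inference.

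One might also answer that using different leaders and lecturers deals with the problem. It does not: it spreads leader effects across groups but leaves patients within a group correlated.

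A reader might be tempted by two stronger readings, and the article supports neither. The first is that the t tests are invalid for the arm comparison; the Statistics section calls them descriptive and gives that comparison to ANOVA. The second is that the predictor regression on the total sample is affected even more, because by then every patient has been in a group. For a predictor that varies between patients within groups, the inflation depends on the product of the predictor's and the outcome's ICCs and is close to nil. In simulations with 60 patients in groups of 6, 10 or 15 and ICC 0.05 or 0.10, the type I error stayed at about 0.05 throughout. Only predictors at group or centre level would suffer, and the article names none.

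**Conclusion.** The point holds for the ANOVA comparison of the arms. The named analysis assumes an independence that group delivery is likely to break in the treated arm. On the assumed range, the standard error is understated by a factor of between 1.02 and 1.30, and a nominal 5% test has a true level between about 5.4% and 13%. Where the trial falls in that range depends on a group size and an ICC that the article does not give. It would be wrong to apply the full treated-arm design effect (up to 1 + 14 × 0.10 = 2.4) to the whole comparison, because the waitlist arm is not clustered; the factor for the difference is at most 1.70. It would also be wrong to expect the pilot to deliver a usable ICC. The change is worth making because it is cheap and because the result feeds a decision on a main trial of the same design.

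**What to change.** - Record a therapy-group identifier for every treated patient.
- Present the difference between T2 in the intervention arm and the post-waiting measurement in the waitlist arm with a confidence interval that allows for clustering in the treated arm only. Because groups are few, do this mainly by fixing the ICC at 0.01, 0.05 and 0.10 and showing all three intervals.
- If the number of groups allows, add as support a partially nested mixed model: a random group effect in the treated arm, waitlist patients as singletons, separate residual variances, and Satterthwaite or Kenward–Roger degrees of freedom.
- Report the ICC with its interval as a descriptive result.
- Size the main trial over a range of ICCs, with the design effect on the treated arm, and not from the pilot's unadjusted ANOVA.

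The cost is one variable and a change to the analysis wording; STATA is already named. The downside is wider intervals and an ICC estimate too imprecise to use alone.

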We searched PubMed and PsycINFO and found only one randomized controlled pilot study of psychoeducation for ADHD among adults. In this study [23], a series of 11 psychoeducational sessions related to clear ADHD-specific challenges were compared with cognitive behavioral group therapy. The results indicated that both types of treatments reduced symptom severity and the negative effects of symptoms, diminished hyperactivity and impulsiveness, and improved attention and self-esteem. Patients also reported a decrease in anxiety and depression symptoms; 93.8% of patients completed the intervention. We also found a non-controlled, pilot study of psychoeducational groups for adults with ADHD and their significant others based on elements of CBT, neuropsychology, and results from interdisciplinary ADHD research. The intervention was conducted at three different clinics in Sweden and comprised 41 patients and 40 significant others. The results suggested there is an increase in knowledge of ADHD, quality of social relations, and psychological well-being after treatment [24].

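### The arms are to be compared by ANOVA with no baseline term named, although pre-treatment scores are collected; this costs precision and, if dropout differs by arm, can bias the preliminary effect

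*Protocol article*

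**What the plan says.** The Statistics section lists chi-square and t tests for descriptive work and "analysis of variance (ANOVA) for comparison of results for the control and experimental groups". It does not say whether this means ANOVA of the post score, of change, or of repeated measures, and it names no covariate. Linear regression is mentioned only for predictors in the total sample, which is not an arm comparison.

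Under Data and measurement, scores are taken at T0 (before randomisation), T1 (before the intervention), T2 (after it) and T3 (10 weeks later). The waitlist arm has extra pre-waiting and post-waiting scores. The randomised contrast is therefore arm A at T2 against arm B post-waiting, with two earlier scores per patient available.

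On incomplete data, "Recruitment and dropout rates will be evaluated using absolute and percentage frequencies". The Background treats completion as an open question: "We require information on how many patients will complete the intervention with evaluable data". No dropout rate is assumed. The only completion figure comes from a cited trial, where "93.8% of patients completed the intervention". On size, "the anticipated sample will be 60 patients—30 patients in each arm".

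**The concern.** Earlier scores on the same scales usually predict the post score. An unadjusted comparison leaves that variation in the error term, and with 30 per arm the loss is noticeable. Taking change scores recovers only part of it.

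There is also a conditional risk of bias. ANOVA uses only patients who have the outcome. Arm A attends ten weekly sessions, arm B waits, and the trial is not double-blinded, so loss that differs by arm is plausible. If it also follows observed severity, the remaining patients are no longer comparable at baseline, and an analysis without a baseline term does not correct for this.

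The result is used. Under Main study and decision to proceed, preliminary efficacy on symptoms and quality of life is part of the basis for going on. The Background also wants the pilot to supply parameters for the next sample size calculation.

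**Working it through.** **The plan's own figure.** 30 + 30 = 60 agrees. The Sample size section gives no alpha, power, effect size, SD or dropout, so there is no power calculation to reproduce.

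**Inputs.** From the protocol: 30 per arm, the assessment times, and 93.8% completion in the cited trial. Assumed, because the protocol gives none: SD 1 at each time; correlations T0–T1 0.75, T1–post 0.65, T0–post 0.60; true effect 0.40 SD; and the loss patterns below. T1 stands for arm A at T1 and arm B pre-waiting. Positive bias means that the benefit is overstated.

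**Precision at 20% random loss.** n = 30 × 0.80 = 24 per arm, and SE = √(residual variance × 2/24).

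- Post score: √(1 × 0.0833) = 0.29.
- Change from T0: variance 2(1 − 0.60) = 0.80; √(0.80 × 0.0833) = 0.26.
- Change from T1: variance 2(1 − 0.65) = 0.70; √(0.70 × 0.0833) = 0.24.
- ANCOVA on T0: variance 1 − 0.60² = 0.64; √(0.64 × 0.0833) = 0.23.
- ANCOVA on T0 and T1: R² = (0.60² + 0.65² − 2 × 0.60 × 0.65 × 0.75)/(1 − 0.75²) = 0.1975/0.4375 = 0.45; √(0.55 × 0.0833) = 0.21.

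Simulation, which also pays for estimating the slopes, gives about 0.24 and 0.22 for the two ANCOVAs and 0.24 for the likelihood analysis. In the formula, T0 adjustment is worth 1/0.64 = 1.56 times the patients against the post score, and 0.80/0.64 = 1.25 times against change from T0.

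**Bias when dropout follows severity in arm A only.** 6,000 runs in each of four scenarios. Dropout logit in arm A = −1.6 + (0.7 or 1.2) × (T0 or T1 score), which gives 19–22% loss. In arm B the logit is −2.4, or about 8% at random.

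| Analysis | Bias (SD) | SE (SD) |
|---|---|---|
| ANOVA, post score | +0.07 to +0.14 | 0.27–0.28 |
| ANOVA, change from T0 | −0.01 to −0.09 | 0.25 |
| ANCOVA on T0, completers | 0.00 to +0.05 | 0.23 |
| ANCOVA on T0 and T1, completers | about 0 | 0.21–0.22 |
| Likelihood model, T0, T1 and post, all randomised | about 0 | 0.22–0.23 |

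**When the bias shrinks or remains.**

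- Random loss, even at 20% against 8%, or the same severity-related loss in both arms: bias is zero for every method.
- About 6% loss (100 − 93.8 = 6.2%) with slope 0.7: +0.02 to +0.03 for the post score and 0.00 to −0.02 for change. A steeper gradient raises the post-score figure to about 0.04 to 0.05.
- Loss in arm A driven by the unseen outcome (separate run: effect 0.5 SD, all correlations 0.5, nominal 20% loss): 0.14 for the post score, 0.07 for change, 0.10 for the likelihood model. Adjustment does not cure this case.

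**The case against.** The strongest reply is that this is a condensed article of a pilot sized on practical grounds. The SAP is not shown, and covariates, analysis sets and missing-data rules commonly sit there. Naming ANOVA does not rule out a baseline term. Efficacy is called preliminary, no efficacy threshold is set for proceeding, and the largest bias above is about half a standard error (0.14/0.28).

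Much of this stands. The absence of an imputation rule or analysis set is not an error here, and the effect on the estimate is modest. What remains is that the article does name a method for the arm comparison, and the method as named uses the available baseline poorly.

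Three stronger readings are tempting, and the document does not support them.

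- **That ANOVA inflates the effect.** Bias needs dropout that both differs by arm and is related to outcome. Its sign depends on which ANOVA is meant: in the scenarios tabulated, change scores understate the effect.
- **That leaving out the dropouts wastes their T0 and T1 scores.** Completers adjusted for both scores do as well as the likelihood model on bias and precision. The gain comes from baseline adjustment; the dropouts' own early scores add almost nothing.
- **That the plan expects dropout and excludes those patients.** It intends to measure dropout and states no rate. Exclusion follows from how ANOVA works; the article does not state it.

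**Conclusion.** The point holds as a moderate weakness in a stated method. The firmer part is precision: about 0.29 SD (post score) or 0.26 SD (change from T0) against 0.22 to 0.24 SD with adjustment, at 20% random loss. This requires no informative dropout, only correlations near those assumed. If change is taken from T1, ANOVA reaches about 0.24 SD and the gain is smaller.

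The bias is conditional. It reaches about +0.14 SD (post score) or −0.09 SD (change) with 19–22% severity-related loss in arm A, is small at the loss seen in the cited trial, and is nil when loss is random or alike in both arms. The dropout rates and gradients are assumptions; only the 6.2% figure has a source in the document.

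**What to change.** In the Statistics section, replace the ANOVA with a baseline-adjusted comparison of arm A at T2 with arm B post-waiting, and report the difference with its 95% CI. Either of two forms will do:

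- a linear mixed model for repeated measures with arm, time and arm-by-time, T0 as a common baseline, and all available scores (T0; T1 or pre-waiting; T2 or post-waiting) of every randomised patient in the assigned arm; or
- ANCOVA of the post score on T0 and the T1 or pre-waiting score. Adjusting for T0 alone leaves up to about 0.05 SD of bias when dropout follows the T1 score.

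Only T0 is stated to precede randomisation. If patients know their allocation when the T1 or pre-waiting form is completed, the mixed model is the safer form, because it constrains only T0 to be equal between arms.

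The cost is a change of wording. No new data are needed, and both named packages fit either model. The downside is the assumption that outcomes are missing at random given the observed scores. Bias from loss that depends on the unseen outcome stays, and the report should say so.
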